### Plans to give access to the full protocol, participant level-data and statistical code {31c}

Access to trial data will be made available upon reasonable request to the PI.

## Oversight and monitoring

### Composition of the coordinating center and trial steering committee {5d}

The trial coordination will be in charge of the P.I. and a steering committee will include two additional collaborators.

### Composition of the data monitoring committee, its role and reporting structure {21a}

A data monitoring committee (DMC) composed of three independent external collaborators, including a statistician, will report to the PI and the Research Center on aspects of trial conduct, such as recruitment, identify the need to make adjustments, and analyze for significant outcomes or harm.

### Adverse event reporting and harms {22}

Should any adverse events, unintended effects, or harm be detected, it is the attending physician’s responsibility to report to the PI and the Investigation Centre of CHULC.

### Frequency and plans for auditing trial conduct {23}

The DMC is expected to perform  trial conduct audits once 20 and 40 randomized patients have completed 28-day follow-up and at trial conclusion.

### Plans for communicating important protocol amendments to relevant parties (e.g., trial participants, ethical committees) {25}

Any protocol modifications or amendments must be communicated to the Research Center and Ethics Committee of CHULC.

### Dissemination plans {31a}

The dissemination of the trial results will take place in the form of public presentations and publications in the appropriate scientific media.

## Discussion

This is the first trial to compare the impact of different therapeutic paracentesis strategies on organ dysfunction and outcomes in the prevention and treatment of IAH in critically ill patients with cirrhosis and ascites. Ultimately, we expect to discuss these strategies and improve clinical practice.

Our center has experience in treating critically ill patients with cirrhosis and ascites and IAH and we use both LVP and CPP strategies empirically. The CPP has the potential to minimize IAP, optimize APP, and reduce the number of required abdominal punctures and the risk of perforation and bleeding. However, it may entail higher risk of infection and abdominal wall fistula, when compared to intermittent LVP. The need to better understand the impact of these interventions set the grounds for this trial.

The use of a double lumen catheter for continuous ascitic fluid drainage presents important advantages over a single lumen catheter because: (1) it is more resistant to obstruction by “kinking” due to its internal section pillar and (2) the proximal (lateral) opening is less prone to obstruction by viscera or clotting than the distal (pointing) one. Furthermore, the use of the Seldinger technique to insert the abdominal paracentesis catheter, using an acute angle of percutaneous insertion (ideally, less than 45°), avoiding a perpendicular approach, (1) reduces catheter kinking and (2) may prevent insertion site fistula, given the oblique multiplane closure trajectory. These details are even more important given the duration of the CPP strategy.

The use of IAPC in patients with cirrhosis and ascites has been demonstrated to be safe and effective outside of the ICU setting [20–22]. We do not use prophylactic antibiotics associated with paracentesis in this trial nor in our usual clinical practice. Similarly, in the prevention of catheter-related bloodstream infections, the use of prophylactic antibiotics is not recommended in the clinical management of non-tunneled central venous catheters [28]. Additionally, the use of prophylactic antibiotics in the intervention arm would create a important therapeutic differences between study groups and hinder the comparison of results.

Possible limitations in our trial protocol include the following: (1) underpowered sample size to identify significant differences for some secondary outcomes and paracentesis-related complications or harm; (2) reduced generalizability of results due to the single-center, specialized liver disease ICU setting; (3) selection bias due to the fixed block size randomization; for this reason, the group allocation will be revealed by the attending physician, rather than the P.I.; (4) clinical reasons may induce protocol non-adherence or violation, although this may reflect real-world conditions and improve generalizability of results.

Finally, we chose serum creatinine as the primary outcome variable to compare trial groups since it remains the most practical biomarker of renal function in patients with AKI [13]. Even though serum creatinine has some limitations, particularly regarding interpretation in the individual cirrhotic patient, the randomization process should homogenize patient characteristics at baseline and allow for the comparison of results between groups.

This research trial conforms with the ethical norms and standards in the Declaration of Helsinki, including local Ethics Committee (reference no. 632/2018, 11/02/2022) and registration (ClinicalTrials.gov NCT04322201). This trial has received internal funding granted from the Research Center (reference FFI 06/2019), exclusively for specific laboratory analysis described in the trial protocol.

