## Methods

### Trial design {8}

#### Trial design

This is an investigator-initiated, single-site, open label, randomized clinical trial with parallel group allocation ratio of 1:1 to assess for efficacy and safety.

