### Sample size {14}

The sample size was calculated using the statistical noncentral *t *function, with a one-sided alpha level of 0.05 [31]. The calculations were based on the expected renal function and IAP variation between groups, since we assume the former to be dependent of the latter.

To support the trial rationale of an expected clinically significant IAP decrease of 3 mmHg in the intervention group, a total of 44 patients are considered necessary to detect a statistically significant difference, with 1:1 allocation ratio, 80% statistical power, and 95% confidence level. This estimate is based in a post-hoc analysis of 61 patients with cirrhosis from a multicentric randomized controlled trial in shock patients where a mean difference in IAP of 3 mmHg was found between survivors and non-survivors (13.7 ± 3.9 and 16.7 ± 3.9 mmHg, respectively) [4].

Regarding the primary outcome, to detect a clinically and statistically significant decrease in serum creatinine of 0,4 mg/dL in the intervention group, a total of 60 patients is estimated, with a 1:1 allocation ratio, 95% statistical power, and 95% confidence. This estimate is based on a multicentric observational study of acutely decompensated patients with cirrhosis. In this study, cirrhotic acute-on-chronic liver failure patients with at least one organ failure had a mean creatinine difference of 0,4 mg/dL between survivors and non-survivor groups (0.9 ± 0.45 and 1.3 ± 0.48 mg/dL) [32].

We arbitrarily estimate that protocol non-adherence/attrition or violation after randomization may affect approximately 15% of cases and, therefore, to ensure that the number of patients that complete the protocol is reached for the primary outcome, the total sample size is set at 70 patients with a 1:1 group allocation ratio.

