## Assignment of interventions: allocation

### Sequence generation {16a}

The patient allocation method consists of stratified randomization with blocks within each subgroup. This method is particularly useful with randomizing small samples due to the ability to create balanced groups regarding predetermined variables or characteristics at the beginning of the trial, reducing differences in baseline trial groups characteristics’ that could harm later result analysis and conclusions.

In this small sample size trial, patients will be stratified according to maximum serum creatinine and maximum IAP, expected to be the two most important variables to balance between trial groups at baseline. Stratified randomization will homogenize trial groups ad initio to reduce the probability of unbalanced baseline group characteristics and biased results.

The stratification process will use two strata, namely, maximum IAP and maximum serum creatinine, thus creating four subgroups (I–IV): (I) IAP < 16 mmHg + serum creatinine < 1.5 mg/dL, (II) IAP < 16 mmHg + serum creatinine ≥ 1.5 mg/dL, (III) IAP ≥ 16 mmHg + serum creatinine < 1.5 mg/dL, and (IV) IAP ≥ 16 mmHg + serum creatinine ≥ 1.5 mg/dL [4, 13]. Each subgroup (I–IV) contains sequential blocks of randomized trial group allocation (A) control and (B) intervention, with a 1:1 ratio (i.e., *AABB*, *ABAB*, *BABA*, *BBAA*), as exemplified in Table 1.

**Table 1 Tab1:** Stratification subgroups (I-IV) created using maximum intra-abdominal pressure (IAP) and serum creatinine as strata. Example of stratified randomization with blocks within each subgroup (A, B)

Stratification subgroups (I–IV)	Creatinine < 1.5 mg/dL	Creatinine ≥ 1.5 mg/dL
IAP < 16 mmHg	I) ABAB, ABBA,…	III) BABA, BBAA,…
IAP ≥ 16 mmHg	II) BABA, AABB,…	IV) BBAA, BAAB,…

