### Concealment mechanism {16b}

The adopted concealment mechanism of the allocation sequence will use sequentially numbered (#), opaque, sealed envelopes, and the random sequence for trial group allocation in blocks will be generated by the P.I. using an online tool [33].

To prevent biased selection of patients, the PI will remotely screen for new patient admissions and alert the ICU staff for possible candidates. The patient’s attending physicians are responsible for applying protocol, deciding patient eligibility, and checking for inclusion/exclusion criteria and obtaining the informed consent.

Once patient enrollment has been established, the attending physicians, who are blinded for the allocation blocks, will determine the corresponding stratification subgroup by using IAP and creatinine values and open the respective sealed envelope containing the group allocation. The PI will provide any required assistance, and, finally, be informed of the patient allocation.

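### Fixed blocks of four in an open-label, single-site trial leave about 30% of allocations deducible by the physician who enrols, and the stated safeguards do not prevent it

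*Protocol article*

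**What the plan says.** All references are to the protocol article.

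- **Design.** Trial design {8}: "This is an investigator-initiated, single-site, open label, randomized clinical trial with parallel group allocation ratio of 1:1". Section 17a adds that clinical staff are not blinded to the assigned treatment.
- **Sequence.** Section 16a: "The stratification process will use two strata, namely, maximum IAP and maximum serum creatinine, thus creating four subgroups (I–IV"). Blocks run within each subgroup, and every block shown has length four. The text lists AABB, ABAB, BABA and BBAA. Table 1 also shows ABBA and BAAB.
- **Who generates it.** Section 16b: "the random sequence for trial group allocation in blocks will be generated by the P.I. using an online tool". The P.I. also screens admissions remotely, alerts staff to candidates, helps if required, and is told the allocation last.
- **Who enrols and allocates.** Section 16b: "attending physicians are responsible for applying protocol, deciding patient eligibility, and checking for inclusion/exclusion criteria". The same physicians obtain consent, determine the stratum and, under section 16c, open the lowest-numbered envelope for it. Section 16b says they are blinded to the blocks.
- **Discretion in eligibility.** The exclusion criteria include futility as judged by the medical staff and a predictably short ICU stay (under 72 hours).
- **The admitted limitation.** The Discussion names "selection bias due to the fixed block size randomization; for this reason, the group allocation will be revealed by the attending physician" instead of by the P.I.

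**The concern.** A fixed block size causes selection bias when the person deciding whether to enrol can work out what comes next. The Discussion names that bias, but its remedy deals with a different risk, namely that the P.I. knows the list. The envelope goes to the physician who makes the eligibility judgement, so the route from foresight to selective enrolment stays open.

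Blinding to the blocks is weak protection here. Continuous drainage and intermittent paracentesis look different at the bedside, and there is one unit. The lowest available envelope number also hints at the position within a block. In addition, this article prints blocks of four while recruitment is planned to run until July 2025 (Trial status).

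Two exclusion criteria rest on clinical judgement. The Discussion says the centre uses both methods empirically and describes expected advantages and risks of each, so preferences among staff are plausible. If patients with a poorer outlook are held back when one arm is foreseen, the arms differ at baseline in ways that may not be recorded.

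**Working it through.** The plan gives no figure for predictability, so there is none to reproduce.

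**Inputs.** From section 14: "the total sample size is set at 70 patients with a 1:1 group allocation ratio". From section 16a: block length 4, four strata, and all six balanced sequences (Table 1 alone shows ABAB, ABBA, BABA, BBAA, AABB and BAAB). Two assumptions are needed. The observer knows the block length and the earlier allocations in the stratum. The split of patients over strata is not stated, so I take 17/17/18/18 and then the range over all splits.

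**Step 1. Certain allocations per complete block.**
- Positions 1 and 2: never certain.
- Position 3: certain only if the first two match (AA or BB), in 2 of 6 sequences = 1/3.
- Position 4: always certain.
- Sum = 0 + 0 + 1/3 + 1 = 4/3 of 4 = 33.3%.

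**Step 2. Correct best guesses per complete block.**
- Position 1: 1/2.
- Position 2: 2/3.
- Position 3: (1/3 × 1) + (2/3 × 1/2) = 2/3.
- Position 4: 1.
- Sum = 17/6 = 2.833 of 4 = 70.8%, against 50% by chance.

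**Step 3. Seventy patients in four strata.** A stratum of 17 has four full blocks plus one patient; a stratum of 18 has four full blocks plus two. The leftover patients are never certain.
- Certain: 4 strata × 4 blocks × 4/3 = 21.3; 21.3/70 = 30.5%.
- Best guess, stratum of 17: 4 × 2.833 + 0.5 = 11.83. Stratum of 18: 4 × 2.833 + 0.5 + 0.667 = 12.5. Total = 2 × 11.83 + 2 × 12.5 = 48.67; 48.67/70 = 69.5%.
- Over every split of 70 into four strata: certain 29.5% to 32.4% (20.7 to 22.7 patients); best guess 69.3% to 70.5%.

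**Step 4. Effect of varied block sizes.** Simulation of 2,000 sequences per setting, strata of 17 and 18. The observer knows which sizes are in use but not their order.

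| Block sizes | Certain | Best guess right |
|---|---|---|
| 4 (as planned) | 29.5–31.3% | 69.4–69.5% |
| 4, 6 | 5.6–5.7% | 67.7–68.3% |
| 2, 4, 6 | 3.7% | 68.9–69.6% |
| 4, 6, 8 | 2.2% | 66.4–66.9% |

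Varying the blocks removes nearly all certainty but little of the guessability.

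**Step 5. Subgroup labels in section 16a.**

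| Subgroup | Text | Table 1 |
|---|---|---|
| II | IAP < 16, creatinine ≥ 1.5 | IAP ≥ 16, creatinine < 1.5 |
| III | IAP ≥ 16, creatinine < 1.5 | IAP < 16, creatinine ≥ 1.5 |

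The two definitions are reversed.

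**The case against.** The plan is not careless about concealment. It uses opaque, sealed, sequentially numbered envelopes and says that physicians are blinded to the blocks. The P.I. screens only remotely, leaves eligibility and consent to the physicians, and learns the allocation last. Keeping the list-holder away from the envelope is a real safeguard. Sections 13 and 16b already place consent and enrolment before opening. The authors also disclose the bias. All of this stands, and it narrows the point to deduction by the enrolling physician.

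Prediction also takes effort. At 70 patients in 36 months, accrual is about two a month over four strata (70/36 = 1.9), so each stratum would receive a patient roughly every two months if they filled evenly. Nothing says that physicians keep a running record by stratum. This too stands: the figures describe what a tracking observer could know, not what anyone does.

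Three stronger readings are tempting but not supported:

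- A reader might take the four sequences listed in the text as the only ones in use. Half of each complete block would then be certain (35 of 70, or 32 of 70 at 17/17/18/18) and 75% of best guesses right. Table 1 prints the other two sequences, so the six-sequence case applies. Allowing for incomplete blocks, the certain share in that case stays just below one third.
- A reader might conclude that no analysis could repair the damage. Stratification balances baseline creatinine and IAP, and section 20a plans multivariable models. These limit the harm, though they cannot correct selection on unrecorded judgement.
- A reader might infer from the II/III reversal that envelopes are drawn from the wrong stratum. Strata are assigned from the measured values, Table 1 is captioned as an example, and nothing shows conflicting labels on the envelopes.

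**Conclusion.** The point holds as a vulnerability in allocation concealment that should be corrected. It is not evidence of misconduct or of bias that has occurred. The remedy offered in the Discussion does not treat the problem it names, and blinding physicians to the blocks does not stop deduction from visible earlier allocations once the block length is in print. For a physician who tracks a stratum, about 30 to 32% of allocations (about 21 to 23 of 70) would be certain and about 70% of best guesses right. This rests on six sequences of length four, four strata, and an observer who knows both the block length and the earlier allocations. Without such tracking the exposure is smaller. The subgroup numbering is a separate labelling error.

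**What to change.** For patients still to be randomised:

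1. Reissue the envelopes in each stratum with randomly varied block sizes, for example 4 and 6, or 4, 6 and 8. Do not disclose the sizes or their order to staff who enrol.
2. Have the new sequence generated and sealed by the external statistician already on the data monitoring committee, or by the Research Center, rather than by the P.I., who flags candidates to the staff.
3. Use one numbering for subgroups II and III in the text, Table 1 and on the envelopes.

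Expected gain: certain allocations fall from about 30% to about 2 to 6%. Best-guess success stays near 66 to 68%, so the change removes certainty and not all guessing.

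Cost: a short amendment and a new set of envelopes. The largest possible imbalance within a stratum at any moment rises from 2 (blocks of 4) to 3 (up to 6) or 4 (up to 8). Treatment, endpoint and sample size are unchanged. The benefit applies only to patients not yet randomised, so it shrinks the later the change is made.

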## Trial status

The present trial protocol corresponds to version 10.4, January 2022, and has been implemented in August 2022. The recruitment process began with the enrolment of the first patient in September 2022 and is expected to be complete in 36 months, by July 2025.

Trial registration: ClinicalTrials.gov NCT04322201. Registered 20/12/2019, https://trialsearch.who.int/Trial2.aspx?TrialID=NCT04322201.

## Data Availability

The PI will oversee the study data sharing processes during and after the trial is complete. To ensure confidentiality, shared data will be blinded of any identifying participant information. The study dataset and materials will be password protected and safeguarded by the PI. The final dataset will be made available upon reasonable request.
